## 9.8. Day 1 - Three-hour post IV iron infusion assessment

MRI scan (up to 1 hour)

- Cine imaging for cardiac structure and function
- Tissue characterisation by R1/R2/R2\* relaxometry of the heart, liver, spleen, blood and skeletal muscle

Blood samples:

- One sample collected for study investigations to measure serum iron indices and serum markers of tissue iron damage.

## 9.9. Subsequent Visits

### 9.9.1. Two weeks (14 days+/-2 days) follow up visit

MRI scan (up to 1 hour)

- Cine imaging for cardiac structure and function
- Tissue characterisation by R1/R2/R2\* relaxometry of the heart, liver, spleen, blood and skeletal muscle

Blood samples:

- One sample collected for study investigations to measure serum iron indices and serum markers of tissue iron damage.

### 9.9.2. Six weeks (42 days+/- 2 days) follow up visit

MRI scan (up to 1 hour)

- Cine imaging for cardiac structure and function
- Tissue characterisation by R1/R2/R2\* relaxometry of the heart, liver, spleen, blood and skeletal muscle

Blood samples:

- One sample collected for study investigations to measure serum iron indices and serum markers of tissue iron damage.

## 9.10. Sample Handling

Study specific blood samples will be taken twice on day 1 (baseline assessment, 3 hour assessment), once on each of the follow up visits (2 weeks and 6 weeks). The total volume of blood will be

approximately 20 mls (5ml each time). Blood samples will be processed immediately at OCMR by a member of the research team to extract serum.

Serum samples labelled only with the participants' number/code will initially be stored in a secure research -80C freezer at OCMR. After the last sample from the last participant has been collected, all the samples will be shipped on dry ice to the [name] Lab at the Department of Physiology Anatomy and Genetics, part of the Medical Sciences Division at the University of Oxford. These samples will be kept in a secure, locked -80 freezer until they are ready to be analysed. Here, samples will be tested together as a single batch for iron indices and markers of tissue iron injury (MDA and 4-HNE) as described above.

Any surplus sample will be stored for potential future ethically approved studies in the UK at the end of the study, subject to participant agreeing to this at the consent stage. Otherwise, after completing the sample analysis for the purpose of the study, any remaining samples will be destroyed. For participants who agree to their samples being used in future research, the consent form will be held until the samples have been used up. Only the study team and other delegated members specified in the investigator site file will have access to the samples. A dedicated SOP for sample handling and processing will be followed.

#### **9.11. Early Discontinuation/Withdrawal of Participants**

During the course of the study a participant may choose to withdraw early from the study treatment at any time. This may happen for several reasons, including but not limited to:

- The occurrence of what the participant perceives as an intolerable AE.
- Inability to comply with study procedures
- Participant decision

Participants who withdraw on day 1 will still receive their intravenous iron infusion as per standard clinical care, but no further data or blood will be collected for the purposes of the study. Any data or study blood sample collected up to the point of withdrawal will be retained for use in the study analysis, unless the participant specifically requests that they are destroyed. No further data or samples would be collected after withdrawal.

In addition, the Investigator may discontinue a participant from the study at any time if the Investigator considers it necessary for any reason including, but not limited to:

- Ineligibility (either arising during the study or retrospectively having been overlooked at screening)
- Significant protocol deviation
- Clinical decision

Participants who withdraw before completing day 1 will be replaced with newly recruited eligible participants. Participants who withdraw after completing day 1 will not be replaced.

The type of withdrawal and reason for withdrawal will be recorded in the Case Report Form (CRF).

### 9.12. Definition of End of Study

The end of study will be when the last sample from the last recruit has been analysed.

## 10. SAFETY REPORTING

### 10.1. Definition of Serious Adverse Events

A serious adverse event is any untoward medical occurrence that:

- results in death
- is life-threatening
- requires inpatient hospitalisation or prolongation of existing hospitalisation
- results in persistent or significant disability/incapacity
- consists of a congenital anomaly or birth defect.

Other 'important medical events' may also be considered a serious adverse event when, based upon appropriate medical judgement, the event may jeopardise the participant and may require medical or surgical intervention to prevent one of the outcomes listed above.

NOTE: The term "life-threatening" in the definition of "serious" refers to an event in which the participant was at risk of death at the time of the event; it does not refer to an event which hypothetically might have caused death if it were more severe.

### 10.2. Reporting Procedures for Serious Adverse Events

A serious adverse event (SAE) occurring to a participant should be reported to the REC that gave a favourable opinion of the study where in the opinion of the Chief Investigator the event was 'related' (resulted from administration of any of the research procedures) and 'unexpected' in relation to those procedures. Reports of related and unexpected SAEs should be submitted within 15 working days of the Chief Investigator becoming aware of the event, using the HRA report of serious adverse event form (see HRA website).

## 11. STATISTICS AND ANALYSIS

The plan for the statistical analysis of the study are outlined below. There is not a separate SAP document in use for the trial.

### 11.1. Description of the Statistical Methods

The primary outcome is the absolute change from baseline in MR relaxivities R1, R2, R2\* at each timepoint post Ferinject infusion, according to the following formulae:

$$\Delta R1 = R1 \text{ (at timepoint x)} - R1 \text{ (at baseline)}$$

$$\Delta R2 = R2 \text{ (at timepoint x)} - R2 \text{ (at baseline)}$$

$$\Delta R2^* = R2^* \text{ (at timepoint x)} - R2^* \text{ (at baseline)}$$

R1, R2, R2\* values are calculated as inverse of T1, T2, T2\* relaxation times obtained by the MR relaxometry or mapping techniques. The results will be reported as time series of average values and standard deviations (median and IQR for nonparametric variables) at each timepoint post Ferinject infusion. The presence of statistically significant signal will be assessed using ANOVA.

The secondary outcome measure is the change from baseline in serum concentrations of iron indices (iron, transferrin saturation, ferritin and non-transferrin bound iron) and markers of tissue iron toxicity (MDA and 4-HNE). Results will be expressed both as absolute change from baseline and as percentage change relative to baseline.

Further exploratory analyses will be performed for possible interactions between the observed measures using correlations, crosscorrelations and pharmacodynamic modelling.

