**Key question with safety implications**- We do not know how I.V iron formulations affect myocardial iron levels and cardiac function in the long term. Answering these questions is important for ensuring that correction of iron deficiency is not accompanied by myocardial iron toxicity. It is widely assumed that I.V iron formulations such as Ferinject (ferric carboxymaltose or FCM) are taken up and degraded by macrophages, allowing slow and controlled release of iron into the circulation, and subsequent loading onto the plasma iron chaperone transferrin for uptake by tissues. Most tissues can prevent excess iron accumulation by downregulating the levels of transferrin receptor expression (this is achieved through the iron-sensing function of iron-regulatory proteins IRPs). However, kinetic studies of plasma iron indices, together with the speed of manifestation of associated physiological effects demonstrate that FCM infusion results in rapid and physiologically-relevant rise in non-transferrin bound iron (NTBI) in the plasma. Excess NTBI in the plasma is dangerous because it is taken up by tissues through L-type and T-type calcium channels, which are not regulated by IRPs. These channels are highly expressed in the heart and it is well established that they are responsible for the iron overload cardiomyopathy that occurs in genetic disorders of iron overload such as hemochromatosis (where NTBI is also raised). In pre-clinical mouse models, we found that a patient-equivalent dose of intravenous iron resulted in ~400% increase in cardiac iron levels.

**Study rationale** - This is a pump-priming study to establish if the standard intravenous iron treatment, given as part of standard clinical care to correct iron deficiency, results in an acute rise in tissue iron levels, including myocardial iron at the early timepoints, which would be evidence for the direct, rapid unregulated route of iron uptake. It is an observational cohort study measuring changes in tissue iron levels from baseline following infusion of intravenous iron. Tissue iron levels will naturally vary between individuals. Because of this, the study will not use a placebo arm. Instead, it will measure changes against baseline tissue iron levels.

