### **11.6. The Level of Statistical Significance**

Tests will be two-sided and considered to provide evidence for a significant difference if p-values are less than 0.05.

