**23. APPENDIX B: SCHEDULE OF STUDY PROCEDURES**

| Procedures             | Screening  | Baseline (OCMR)                     | Timepoint 1 (OCMR)                    | Timepoint 2 (OCMR)                         | Time point 3 (OCMR)                        |
|------------------------|------------|-------------------------------------|---------------------------------------|--------------------------------------------|--------------------------------------------|
|                        |            | Day 1 - prior to Ferinject infusion | Day 1- 3hours post Ferinject infusion | Day 14 (+/- 2days) post Ferinject infusion | Day 42 (+/- 2 days post Ferinject infusion |
| Eligibility check      | X          |                                     |                                       |                                            |                                            |
| Informed consent       | X (verbal) | X                                   |                                       |                                            |                                            |
| Demographics           |            | X                                   |                                       |                                            |                                            |
| Medical history        |            | X                                   |                                       |                                            |                                            |
| Research blood samples |            | X                                   | X                                     | X                                          | X                                          |
| Clinical data          |            | X                                   |                                       |                                            |                                            |
| MRI scan               |            | X                                   | X                                     | X                                          | X                                          |

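### Cross-correlation is named for four very unequally spaced visits: its lag has no meaning there, and at lag zero a shared response to the infusion can pass for a link between measures

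*Protocol*

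**What the plan says.** After defining the primary and secondary outcomes as changes from baseline, Protocol Section 11.1 adds: "Further exploratory analyses will be performed for possible interactions between the observed measures using correlations, crosscorrelations and pharmacodynamic modelling". It does not state the lags, whether individual or group series are used, or whether the mean response at each visit is removed first. For the MRI outcomes the same section says "The results will be reported as time series of average values and standard deviations", so a series of group means is one possible input.

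The schedule is fixed elsewhere. Section 9.10: "Study specific blood samples will be taken twice on day 1 (baseline assessment, 3 hour assessment), once on each of the follow up visits". Appendix B gives the first post-infusion point as "Day 1- 3hours post Ferinject infusion". Section 9.9.1 is headed "Two weeks (14 days+/-2 days) follow up visit", and Section 9.9.2 sets the last visit at 42 days with the same window. MRI follows the same four times.

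Every participant receives one infusion, and Section 5 says that "the study will not use a placebo arm". Section 11.6 sets the test rule without exempting exploratory tests: "Tests will be two-sided and considered to provide evidence for a significant difference if p-values are less than 0.05". Section 11 says that no separate SAP is in use, and Section 11.8 says that the outline in the protocol will be followed.

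**The concern.** What cross-correlation adds to ordinary correlation is the lag: it asks whether one series leads another by a fixed interval. That needs a regular time grid and a reasonably long series, and this schedule provides neither.

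At lag zero there is a second difficulty. If two measures both move after the infusion, their time courses resemble each other in every participant, even when one person's response in the first measure says nothing about that person's response in the second. With no untreated group and no stated removal of the visit mean, a test on such series cannot separate a shared reaction to the infusion from a link between the measures.

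This sentence contains the only planned analyses that could connect the serum markers to the organ MRI changes. Section 2 says that the study will inform a larger study of possible toxic effects. A lag read as an order of events, or a shared time course read as a serum marker following organ iron, could be carried into that design.

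**Working it through.** The protocol gives no correlation, effect size or power figure (Section 11.2 says that the sample size of 12 was not derived statistically), so there is no figure of its own to reproduce.

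**1. Spacing (no assumptions).** The times are 0, 3 h = 0.125 d, 14 d and 42 d. The gaps are 0.125 d, 14 - 0.125 = 13.875 d, and 42 - 14 = 28 d. Dividing by 0.125 gives a ratio of 1 : 111 : 224. One visit step therefore has three very different lengths.

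**2. Number of pairs (no assumptions).** Four points give 4 pairs at lag zero and 3 at lag one. Changes from baseline leave three informative points, so lag one has 2 pairs. A correlation on two pairs is always +1 or -1 (ties aside).

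**3. Significance thresholds.** For n pairs the two-sided 0.05 limit is |r| = t/√(t² + n - 2), with t the 97.5% point on n - 2 degrees of freedom.

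| Pairs | Where it applies | Critical \|r\| |
|---|---|---|
| 3 | one series pair, lag one | 0.997 |
| 4 | one series pair, lag zero | 0.950 |
| 12 | across participants at one visit | 0.576 |

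At lag one a single pair of series hardly ever reaches significance, and the result has no fixed meaning if it does.

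**4. Lag zero with a shared response (assumptions needed).** The protocol gives no response shape, response size or SD. Simulation: 12 participants, 4 visits, 20,000 studies per scenario, residual SD 1, between-person SD 1, response varying between people with a CV of 30%. The two measures are independent except that both may respond to the infusion. Shapes are an early peak, a middle peak, a late rise or a step. Entries are the share of studies with p < 0.05.

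| Scenario | Per-person r, tested across 12 | Correlation of the two group-mean series |
|---|---|---|
| No response | about 5% | about 5% |
| Same shape, peak 1 SD | 11-17% | 15-22% |
| Same shape, peak 2 SD | 59-81% | 46-60% |
| Same shape, peak 3 SD | 95-99% | 74-87% |
| Different shapes, peak 2 SD | 8-31% | 0-1% |

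A case that can be repeated exactly: both measures follow the mean course (0, 1, 0.7, 0.5) times the peak, with no variation in response between people. The per-person test then links them in about 12% of studies at 1 SD, 72% at 2 SD and over 99% at 3 SD. With courses (0, 1, 0.3, 0) and (0, 0.3, 1, 0.8) at 2 SD, the rate is about 7%.

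**5. The alternatives.** Correlating changes at one visit across participants, or correlating values after removing the visit mean, gave 4.5-5.3% in every scenario of the table.

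**The case against.** The strongest reply is that the analysis is exploratory, decides no primary or secondary outcome, and is described too loosely to be faulted for a particular calculation. Much of this stands. The plain correlations named in the same sentence can be done validly as written, for example on changes at one visit. Pharmacodynamic modelling can use actual times and has neither problem. The protocol does not propose pooling all person-visits as independent observations, and it should not be criticised as if it did.

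A reader might infer that the plan will report links between unrelated measures because all of them respond to the infusion. The documents do not support that. Whether the organs respond acutely is what the study sets out to learn. With no response the false-link rate is about 5%. With different shapes it is lower than with the same shape, and group means are then hardly ever flagged because four points need |r| above 0.950. A high correlation on three or four points is also not in itself a false positive.

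It can further be said that similar group time courses are of interest in a study of kinetics, and that adjusting for timepoint removes them. That is fair, and it is a reason to show the courses side by side descriptively.

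The reply does not rescue the lag. Its lack of meaning follows from the visit times alone. Nor is this a detail left to another document, since Section 11 says that there is none.

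**Conclusion.** The point holds in a limited form, and its severity is minor. Lagged cross-correlation cannot be interpreted on this schedule; that rests only on the visit times and the pair counts.

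The lag-zero problem is conditional. It needs both measures to respond with similar time courses, and the analysis not to remove the average visit response. Where those conditions hold, the per-person test declares unrelated measures linked in about 11-17% of studies at a peak of 1 within-person SD and 59-81% at 2 SD, against a nominal 5%. These rates rest on assumed shapes, SDs and response sizes and show an order of magnitude only. Section 5 expects a rapid rise in plasma non-transferrin-bound iron and asks whether tissue iron also rises early. The conditions are therefore plausible for some pairs of measures, but the documents do not establish them.

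**What to change.** In Section 11.1 delete crosscorrelations from the list and add text such as:

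> Associations between measures will be estimated (a) across participants, as the rank correlation of the changes from baseline at each post-infusion timepoint (up to 12 participants), and (b) within participants, by a model with participant and timepoint as factors, so that the average response to the infusion is removed. Estimates will be given with 95% confidence intervals and labelled exploratory. Group-mean time courses may be shown side by side descriptively.

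The number is up to 12 because Section 9.11 does not replace participants who withdraw after day 1. Pharmacodynamic modelling with actual times can stay as it is.

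The cost is a few sentences, with no extra scans, samples or participants. The price is that statements about which measure leads are given up, and that intervals will be wide: with 12 participants |r| must exceed about 0.58 to reach significance.

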### **11.2. Sample Size Determination**

The sample size of 12 participants was not arrived at statistically, due to lack of information on the magnitude of effects of Ferinject on R1/R2/R2\* values at early timepoints. However, an exploratory study of MRI imaging following intravenous infusion with ultrasmall superparamagnetic particles of iron oxide (USPIO) at later timepoints used sample sizes of 5-12 participants per group. Of note, the longitudinal design involving repeated measures will increase the statistical power of the study.

### **11.3. Analysis populations**

All participants will be included in the analysis as enrolled.

### **11.4. Decision points**

After the first cohort (3 participants), we will conduct an interim analysis to ensure appropriateness of chosen timepoints.

### **11.5. Stopping rules**

There are no formal stopping rules for this study.

### **11.6. The Level of Statistical Significance**

Tests will be two-sided and considered to provide evidence for a significant difference if p-values are less than 0.05.

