## 6. OBJECTIVES AND OUTCOME MEASURES

| Objectives                                                                                                                                                                                                                    | Outcome Measures                                                                                                                                                                                                                                                                                                               | Timepoint(s) of evaluation of this outcome measure (if applicable)                                                                                          |
|-------------------------------------------------------------------------------------------------------------------------------------------------------------------------------------------------------------------------------|--------------------------------------------------------------------------------------------------------------------------------------------------------------------------------------------------------------------------------------------------------------------------------------------------------------------------------|-------------------------------------------------------------------------------------------------------------------------------------------------------------|
| Primary Objective
To establish the kinetics of iron uptake into the heart, liver, spleen, kidney, skeletal muscle and blood following a single intravenous iron infusion (Ferric carboxymaltose, Ferinject, 1000mg) | Changes from baseline in cardiac structure and function (Cine MRI) and multi-organ magnetic resonance relaxometries ( $\Delta R1/R2/R2^*$ ) for each participant                                                                                                                                                               | Baseline, prior to infusion (day 1)
Timepoint 1- 3hr post infusion (day 1)
Timepoint 2- ~2 weeks post infusion
Timepoint 3- ~6 weeks post infusion |

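### Cine measures are primary in the synopsis and Section 6 but not in Section 11.1, and the multi-organ relaxometry outcome is tested at p<0.05 with no ranking or multiplicity adjustment

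*Protocol*

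**What the plan says.** **Objectives.** Section 6 states the primary objective as "To establish the kinetics of iron uptake into the heart, liver, spleen, kidney, skeletal muscle and blood". Its primary outcome measure is "Changes from baseline in cardiac structure and function (Cine MRI) and multi-organ magnetic resonance relaxometries", assessed at baseline, 3 hours, about 2 weeks and about 6 weeks. The synopsis (Section 3) says the same.

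**Analysis.** Section 11.1 says "The primary outcome is the absolute change from baseline in MR relaxivities" R1, R2 and R2*, at each post-infusion timepoint, and does not mention cine. It names ANOVA as the way to judge whether there is a signal, without saying whether that means one ANOVA per tissue and rate across time or a test at each timepoint. The secondary outcomes in Section 11.1 are serum measures only.

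**Decision rule.** Section 11.6 makes tests two-sided and "considered to provide evidence for a significant difference if p-values are less than 0.05". No adjustment, ordering or descriptive status is attached to any test.

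**Where else it could be settled.** Section 11 states that no separate SAP is in use. Section 11.8 says the protocol's outline will be followed and deviations reported.

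**Tissues.** Kidney is in the primary objective and in the target organs of Section 7, but the visit procedures in Sections 9.7 to 9.9 list "relaxometry of the heart, liver, spleen, blood and skeletal muscle" without it.

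**The concern.** There are two linked problems.

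First, the protocol gives two definitions of its primary outcome. Under one of them a component (cine) has no analysis, and no cine variable is named. A report could follow either definition and claim to follow the protocol.

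Second, within relaxometry every tissue, rate and timepoint has equal standing, and each test below 0.05 is read as evidence of a difference. With this many tests, an isolated significant organ or rate is weak evidence of uptake, but the stated rule does not treat it as weak. Since the results are meant to inform a larger study of possible toxicity, a chance finding in one organ could steer that design. The study is also unblinded (Section 9.5), and the interim look after cohort 1 is meant to check the chosen timepoints (Section 11.4). Emphasis could therefore be settled after data have been seen.

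**Working it through.** The protocol gives no test count, family-wise error rate or power, and Section 11.2 says the sample size of 12 was not derived statistically. There is no stated figure to reproduce.

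**Step 1: set the definitions side by side.**

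| Place | Relaxometry primary? | Cine primary? | Cine analysis given? |
|---|---|---|---|
| Sections 3 and 6 | Yes | Yes | Not applicable |
| Section 11.1 | Yes | Not mentioned | No |
| Rest of Section 11 | – | Not mentioned | No |

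**Step 2: count the family.** Inputs: 6 tissues (Section 6) or 5 (Sections 9.7 to 9.9, no kidney); 3 rates (Section 11.1); 3 post-baseline timepoints (Section 6).

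- Each timepoint tested: 6 × 3 × 3 = 54, or 5 × 3 × 3 = 45.
- One ANOVA across time per tissue and rate: 6 × 3 = 18, or 5 × 3 = 15.

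**Step 3: error rate if tests are independent.** With k tests at 0.05 and no true change, P(at least one p<0.05) = 1 − 0.95^k, and the expected number of false positives is 0.05k.

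| k | P(at least one) | Expected false positives |
|---|---|---|
| 15 | 53.7% | 0.75 |
| 18 | 60.3% | 0.90 |
| 45 | 90.1% | 2.25 |
| 54 | 93.7% | 2.70 |

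**Step 4: allow for correlation.** The protocol gives no correlations, so a common correlation between the tissue-rate series was assumed and varied. Null data were simulated for 12 participants at 4 timepoints (4,000 runs per setting). They were analysed either by one repeated-measures ANOVA per series or by paired t-tests of each timepoint against the shared baseline. Chance of at least one p<0.05:

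| Assumed correlation | 15 ANOVAs | 18 ANOVAs | 45 t-tests | 54 t-tests |
|---|---|---|---|---|
| 0 | 54% | 61% | 88% | 92% |
| 0.3 | 47% | 52% | 81% | 86% |
| 0.5 | 39% | 42% | 72% | 75% |
| 0.7 | 28% | 32% | 58% | 63% |
| 0.9 | 16% | 17% | 35% | 37% |

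The t-test columns fall slightly below the independence figures even at correlation 0, because the three changes in a series share one baseline. The lowest entry, 16%, is about three times the nominal 5%. Cine measures are not counted and could only add to the family.

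**The case against.** **The 54-test count.** A reader might infer that the protocol plans 54 separate tests with a 94% chance of a false positive. It does not say so. It defines 54 changes and names ANOVA, which most naturally means 18 omnibus tests, or 15 without kidney. Independence is also the least plausible case, since R1, R2 and R2* are all read as indicators of the same tissue iron. This objection stands: 54 tests and 94% are upper limits. A false positive is more likely than not only for some combinations of test count and correlation.

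**The exploratory aim.** This is a 12-participant pump-priming study reporting time series with means and SDs. The global null is a severe assumption after an iron infusion, and there is no rule that one significant result makes the study positive. Strict family-wise control is therefore partly a matter of judgement, and this part stands too. But Section 11.6 does not label its p-values descriptive; it calls them evidence.

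**A single heart contrast.** A reader might infer from the rationale that myocardial iron at 3 hours is the one real question and should be the sole primary. Section 5 speaks of tissue iron in general, "including myocardial iron at the early timepoints, which would be evidence for the direct, rapid unregulated route of iron uptake". The heart is given as an instance and the timepoints are plural, so no single contrast is singled out. Making one 3-hour heart contrast the only primary would also conflict with the multi-organ kinetics objective.

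**Existing safeguards.** Registration before the first participant and reporting of deviations help, but they cannot resolve two conflicting definitions within the protocol.

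**Conclusion.** The point holds. Cine is primary in Sections 3 and 6, absent from the Section 11.1 definition, and analysed nowhere in Section 11. No tissue, rate or timepoint ranks first, each test is judged at 0.05, and the protocol rules out a separate SAP that could settle either matter.

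The chance of at least one significant result with no true change is about 54% to 94% if tests are independent, depending on whether 15, 18, 45 or 54 tests are run. At an assumed correlation of 0.9 it is about 17% for 18 ANOVAs and 37% for 54 tests. Every case examined exceeds 5%. These figures rest on the global null and on assumed correlations. The conflict over cine and the missing hierarchy depend on neither.

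**What to change.** 1. Make Sections 3, 6 and 11.1 agree by listing cine structure and function as secondary. Name the cine variables and state a change-from-baseline analysis for them.
2. Keep the multi-organ kinetics objective. State in Section 11.1 that one repeated-measures ANOVA is run per tissue and rate, and reconcile kidney between Section 6 and Sections 9.7 to 9.9 so that the family is fixed at 18 or 15.
3. In Section 11.6, report Holm or false-discovery-rate adjusted p-values across that family, give 95% CIs for each timepoint change, and label unadjusted p-values descriptive.
4. Optionally, before any cohort 1 scan is read, name one rate for the heart as the leading test at 0.05, since the heart is the rationale's own example. The choice of rate is the sponsor's.

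**Cost.** No scan, visit or participant is added; this is protocol wording and a small amount of analysis. The downside is that an isolated nominal p<0.05 in one organ can no longer be called evidence of uptake. With Holm, the smallest p-value must fall below 0.05/18 = 0.0028 (0.05/15 = 0.0033 without kidney), which is demanding with 12 participants. That is the reason to consider a named leading test or false-discovery-rate control.
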